### Harms

Potential risks, such as a major cardiac event or a fall, are expected to be rare. The intensity of the exercise proposed in this trial is low to moderate, interspersed with pauses and characterised by a low cardiovascular load. In our experience, among over 2000 patients at high cardiovascular risk with PAD, CKD, diabetes and/or stroke, programmes performing more than 400 000 home walking sessions for 6 months reported no falls or major events. Minor risks of participation, such as muscle soreness, fatigue or minor sprains or strains, are expected to occur in a small number of individuals during the training phase or assessment phase.

Anyway, all necessary procedures for the safety of the enrolled patients will be taken, including the exclusion of individuals with absolute contraindications to testing (inclusion/exclusion criteria) and careful monitoring of the testing phases by trained personnel (licensed and properly trained physical therapists/exercise physiologists). Direct supervision of trained operators will be employed during every phase of testing in which the participant is standing and/or walking. A medical clearance will be requested before initiating the exercise intervention.

Finally, proper insurance has been subscribed to cover all possible harms that may occur.

### Data monitoring, auditing and interim analyses

The study does not have a data monitoring committee. The research coordinator will conduct an interim analysis every 6 months to determine whether the study should be stopped, modified or continued. Any subsequent changes will be discussed by the research team and communicated to the funding agency and the Ethics Committee.

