### Sample size and recruitment

The feasibility of this study is assessed by analysing the prevalence of patients with CKD-PAD in the hospitals involved in this project. We identified a cohort of over 200 patients potentially meeting the inclusion criteria. In each centre, a network of physicians, including nephrologists, internists and vascular surgeons, will be established to identify potentially eligible patients and facilitate enrolment. Every centre will identify a responsible person for enrolment to assess patients’ eligibility and manage their inclusion in the randomisation list.

We calculated the sample size, hypothesising the superiority of the experimental treatment over the control group. A sample of 96 patients, 48 in each group, is needed to detect a 30 m improvement in 6 min walking distance in favour of the experimental group, assuming an SD of improvement of 30 m, with a type I error of 0.05 and a power of 90%. To account for possible dropouts, the sample size will be increased by 30%, resulting in a total of 124 patients to be enrolled.

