### Blinding and data collection, management and analysis

Professionals in the management of the exercise programme will be responsible for outcome measurement, with one researcher assigned to each operational unit. An expert in data collection of body composition and bone mineral density will be responsible for collecting body composition parameters in every operating unit.

Two researchers blinded to the patients’ allocation will be responsible for entering the data into two electronic datasets, which will be compared with check for possible mistakes in data input. A password will protect every data set.

The researchers responsible for the statistical analyses will also be blinded to the patient group assignments. He will also be responsible for data management (quality control and data checking) and data analysis according to the different research hypotheses described.

Patient’s data will be treated following current regulations, including the 2016/679 European Union Act and D.Lgs. 30 June 2003, n. 196 s.m.i. Italian regulation, as well as any possible adjunctive measures deemed applicable by the Italian Data Protection Authority.

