### Statistical methods

Standard methods for the analysis of RCTs will be employed. All analyses will be conducted using intention-to-treat, where any subject randomised to one arm remains in that arm regardless of whether they received the intervention.

Missing values, although we will make any effort possible to reduce their incidence, will be treated using the multiple imputation procedure. Moreover, a sensitivity analysis will be performed to assess the stability of the study’s conclusions, comparing the intention-to-treat analysis with an analysis that takes into account the level of participation in the intervention arm. A p value <0.05 will be considered statistically significant. Several statistical analysis software packages, including SPSS, MedCalc and Stata, will be used.

A Shapiro-Wilk test will verify the nature and distribution of the data. At baseline, the two groups will be compared in terms of demographics and primary and secondary outcome measures. Although our initial hypothesis suggested the superiority of the exercise group over the control group, to account for the possibility that participants in the control group might achieve better outcomes than those in the intervention arm, we will use two-tailed tests of significance for all analyses. For categorical variables, the χ^2^ test or Fisher’s test will be employed, as appropriate. Overtime between-group differences will be analysed using t-tests for symmetrically distributed data and analogous non-parametric tests, such as the Mann-Whitney test, for skewed data. A two-way repeated measures analysis of variance (factors: treatment, time) will be run to compare differences over time for secondary outcomes. Paired-sample t-tests or Wilcoxon tests will assess the within-group variations. Suppose a significantly different distribution between the two groups in the baseline outcome level is identified. In that case, a secondary analysis will be performed using multivariate modelling, such as analysis of covariance, to adjust for these factors. For the long-term outcomes, Kaplan-Meier curves with log-rank tests and Cox proportional hazard regression models will be performed.

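### Six-monthly interim analyses by the research coordinator can stop or modify the trial and are not limited to safety or pooled data; if they compare arms at 0.05, type I error is not controlled at 5%

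*Protocol article*

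**What the plan says.** The article's section on data monitoring, auditing and interim analyses makes three statements. On oversight: "The study does not have a data monitoring committee". On the looks: "The research coordinator will conduct an interim analysis every 6 months to determine whether the study should be stopped, modified or continued". On what follows: "Any subsequent changes will be discussed by the research team and communicated to the funding agency and the Ethics Committee". It does not say which data are examined, or whether they are examined by arm.

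The section on statistical methods sets one threshold, "A p value <0.05 will be considered statistically significant", and adds that "we will use two-tailed tests of significance for all analyses". It does not separate interim from final tests. The sample size section works "with a type I error of 0.05 and a power of 90" per cent, and gives 96 patients as the number "needed to detect a 30 m improvement in 6 min walking distance in favour of the experimental group".

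**The concern.** The article itself fixes the frequency of the looks, their authority over the trial, who performs them and the absence of an independent body. It leaves open whether the coordinator may compare the arms on efficacy. The only significance level in the article is a flat two-sided 0.05. A reader following the text could therefore test 6MWD every 6 months and stop at the first p below 0.05.

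Three things would then be at stake:

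- The false-positive rate for the primary outcome would exceed the 5% assumed in the sample size statement.
- A trial stopped early on such a result would tend to overstate the effect.
- Someone inside the trial team would know how the arms compare while patients are still being enrolled and tested. Changes to the design made with that knowledge would add error that no standard stopping boundary covers.

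**Working it through.** **Inputs from the article.** Two-sided tests at 0.05; power 90%; difference 30 m; SD of improvement 30 m; 48 per arm; 1:1 allocation; primary outcome measured at 6 months (T1); looks every 6 months.

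**Assumed, because not stated.** The length of recruitment (uniform over time), and that every look tests 6MWD by arm at 0.05.

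**1. The plan's own figure.** For two means, n per arm = 2 × (1.960 + 1.282)² × SD² / difference². With SD 30 and difference 30 this is 2 × 10.51 × 1 = 21.0, so 22 per arm, not 48. An SD of 45 m gives 21.0 × 2.25 = 47.3, so 48. That mismatch is a separate matter. It is used here only to give two SD values for the power check in step 5.

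**2. How many looks could carry primary data.** A look at month 6 has almost no T1 results. With recruitment over R months, T1 data are complete at month R + 6, so informative looks fall at months 12, 18, … up to R + 6. That is R/6 looks including the final one, and they are equally spaced if recruitment is uniform.

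- R = 12: 2 looks
- R = 18: 3 looks
- R = 24: 4 looks
- R = 36: 6 looks

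**3. Overall type I error.** With K equally spaced looks, the test statistics at looks j < k have correlation √(j/k). The overall error is 1 − P(|Z₁| ≤ 1.96, …, |Z_K| ≤ 1.96) under no effect. For K = 2 the correlation is √0.5 = 0.707. Results by numerical integration, with a simulation of 1,000,000 trials as a check:

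| Looks (incl. final) | Integration | Simulation |
|---|---|---|
| 1 | 5.0% | – |
| 2 | 8.3% | 8.3% |
| 3 | 10.7% | 10.7% |
| 4 | 12.6% | 12.7% |
| 6 | 15.5% | 15.5% |

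**4. A boundary that restores 5%.** For one interim look at half the T1 data, an O'Brien-Fleming-type spending function with 0.025 in each tail spends 2 × 2 × [1 − Φ(2.241/√0.5)] = 0.0031 at the interim. The critical values are |Z| > 2.963 at the interim (p<0.003) and |Z| > 1.969 at the end (p<0.049). Tested together at 0.003 and 0.049, the overall error is 5.0%.

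**5. Power with that boundary at 48 per arm.** The drift is 30 / (SD × √(2/48)), which is 4.90 for SD 30 m and 3.27 for SD 45 m. Power is 99.8% and 90.3%, so the boundary needs no extra patients.

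**The case against.** The strongest reply is that the article names no interim endpoint, no comparison by arm and no efficacy stopping rule. A decision to stop, modify or continue could rest on safety, recruitment, pooled data or futility, and none of these raises type I error. The 0.05 in the statistical methods is a general statement that does not mention interim looks, and a group-sequential design also quotes an overall 0.05. A boundary may exist in a full protocol or analysis plan that is not shown. All of this stands. It makes the inflation conditional, and the missing boundary is not in itself the finding. What remains is that the article gives an internal role authority to stop or modify the trial without restricting what that role may look at. Any boundary held elsewhere would still have to be reconciled with the flat 0.05.

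Two stronger readings are tempting, and the documents support neither.

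- A reader might infer that the whole study team sees the results. The text says only that subsequent changes are discussed by the research team. Sharing of by-arm figures beyond the coordinator is not stated.
- A reader might infer a contradiction with the blinding section, where "The researchers responsible for the statistical analyses will also be blinded to the patient group assignments". That sentence concerns the statistical analysts. The research coordinator is named as a different role, and pooled or group-coded looks would be compatible with both sections.

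It may also be said that the sample size suffers for lack of an allowance for repeated looks. With an O'Brien-Fleming-type boundary no power shortfall appears, so that argument carries little weight.

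**Conclusion.** The point holds in conditional form. The rule is badly fixed: recurrent looks inside the trial team, with authority to stop or modify, no independent committee and no restriction to non-comparative data, beside a single two-sided 0.05. A reader might conclude that the type I error is above 5%. The article supports only that it is not controlled at 5% if the looks compare arms on 6MWD at 0.05.

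In that case the error is about 8% to 16% for 2 to 6 looks. The range rests on assumed recruitment of 12 to 36 months, equal spacing, and a test at 0.05 at every look. In the same case, one member of the trial team at least would see emerging results by arm. The matter should be settled before any look with T1 data, because a comparative look cannot be undone.

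**What to change.** Rewrite the section on data monitoring, auditing and interim analyses so that the 6-monthly review covers recruitment, adherence, data quality and adverse events only. State that efficacy data will not be compared by arm before the last T1 visit.

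If early stopping for efficacy is wanted, replace the open rule with one pre-specified look at half the T1 data, using an O'Brien-Fleming-type spending boundary (about p<0.003 at the interim and p<0.049 at the end). A person outside the trial team with the skills for such an analysis should hold the by-arm results. The external administrator used for randomisation is not described in terms that show suitability for this. Amend the flat 0.05 in the statistical methods to match.

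The cost is protocol wording. The first option gives up an informal chance to stop early for benefit. The second needs one outside person. Neither needs more patients.

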### Confidentiality

Participant confidentiality will be rigorously maintained throughout all phases of the study. Each participant will be assigned a unique study identification number, and all data will be de-identified before analysis. Personally identifiable information, including names and medical records, will be stored separately from study data in secure, access-restricted databases. Only authorised research personnel will have access to identifiable participant data, and all team members will receive training in confidentiality and data protection procedures. Electronic data will be stored on encrypted and password-protected systems, and any physical records will be secured in locked filing cabinets in restricted-access areas. Data will be used solely for the purposes outlined in the study protocol. No identifiable information will be disclosed in any publication, presentation or report resulting from this research.

### Dissemination

The results obtained from this RCT will be disseminated through multiple channels to ensure that the knowledge generated reaches relevant stakeholders, including the scientific community, healthcare professionals, policymakers and the general public. The primary method of dissemination will be through publication in peer-reviewed scientific journals relevant to the study’s field. Second, results will be presented at scientific conferences. They will be posted on clinical trial registries. Finally, a plain-language summary of the trial findings will be developed for study participants and the general public to be distributed through patient groups, hospital websites and the community.

Patients’ associations will be involved in the discussion of the results obtained after the analyses performed by the research team.

## Conclusions

This study will fill a knowledge gap in the literature as no trials have primarily focused on mobility in patients with concomitant CKD and PAD. This trial will propose a model of a home-based exercise program as a non-invasive alternative to manage the mobility impairment in this population. This type of model may reduce the rate of surgical or endovascular revascularisation and achieve better short-term and long-term clinical outcomes.

This study provides an example of the management of this population by care teams employing a collaborative, multidisciplinary approach, testing the feasibility of this approach in the nephrology departments of five different Italian regions and demonstrating its potential for wider application. In the event of positive results from this rigorously conducted trial, a simple, integrated model of exercise therapy, effective and low-burden for patients and families, will be validated.

The introduction of this model into clinical practice could be beneficial for managing CKD patients with PAD, reducing sedentariness, deconditioning and walking disability, and limiting related clinical and psychological consequences.

In addition, the attempt to slow the decline of renal function and prevent entry into dialysis treatment is a further sanitary, socioeconomic and environmental potential outcome of interest, particularly considering the potential application of this programme in different settings with limited resources. The validation of this feasible exercise programme may be a turning point for the health service, which could employ a cost-effective intervention strategy centred on patient empowerment.

## Data Availability

No data are available.
